### Study aims and objective

This protocol study aims to evaluate an innovative rehabilitation treatment based on robotics, for the older patients with Parkinson’s disease, designed to improve the gait and to reduce the risk of falling. The treatment involves the use of two robotic devices: Tymo system (Tyromotion, Austria), a wirelesss static and dynamic platform, for evaluating and rehabilitating posture, and Walker View (TecnoBody, Italy), a treadmill equipped with a sensorised belt with eight load cells and a 3D camera.

The primary aim is the evaluation of the effect of the rehabilitation treatment on the balance and gait of the older PD patient, as a result of the use of the Tymo system or Walker View, at the end of the treatment and at a 6 months, 1 and 2 years’ follow-up using POMA scale.

The secondary aims are:
the evaluation of the effect of the rehabilitation treatment on the gait speed of the older PD patients, as a result of the use of the Tymo system or Walker View, at the end of the treatment and at a 6 months, 1 and 2 years’ follow-up using instrumental gait analysis;the evaluation of the effect of the rehabilitation treatment on the fear of falling of the older PD patients, as a result of the use of the Tymo system or Walker View, at the end of the treatment and at a 6 months, 1 and 2 years’ follow-up using FES-I short form scale.

In addition, the study design will include use a standardized questionnaires and instrumental gait analysis, in order to collect data on the improvements with a mix-method approach.

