## Methods/design

### Trial design

This study is a single blinded (outcome assessors) randomized controlled trial. One hundred ninety-five patients with PD will be recruited and randomly divided into three groups, to receive a traditional rehabilitation program or, in addition to the traditional therapy, a robotic rehabilitation using Tymo system or Walker View. Assessments will be performed at baseline, at the end of treatment and 6 months, 1 year and 2 years from the end of the treatment. For the duration of the study, patients cannot receive treatments through robotic devices but will continue to be followed as outpatients by our rehabilitation department.

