### Sample size

The Performance-Oriented Mobility Assessment (POMA) [27], a test widely used to assess walking ability and associated with equilibrium, is used to calculate the sample size [28]. Assuming a small effect size of 10% [29], it is estimated that the overall sample size needed to capture this effect size is of 153 subjects, assuming a statistical power of 80%, a significance level of 0.05, three groups and 5 repeated assessments (a baseline and 4 follow-ups) in an ANOVA model within-between interactions. Even assuming a 25% drop out rate, the total number required would be 195 subjects (65 for each arm).

It is hypothesized that this sample dimension is more than sufficient to grasp a variation also for secondary outcomes for which a treatment effect size is assumed of a similar or higher entity than that identified for the primary outcome [30, 31].

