### Recruitment

Patients are selected by the outpatient department at the Clinical Unit of Physical Rehabilitation, IRCCS INRCA, in the Ancona and Fermo branches. These patients are contacted to schedule a visit with the physician. Once the compliance with the inclusion and exclusion criteria of the study has been verified and the informed consent (see Supplementary file) has been obtained in triplicate, the doctor proceeds with the baseline evaluation and with acquisition of gait assessment parameters through Gait Analysis at the Movement Analysis Laboratory of the Clinical Unit of Physical Rehabilitation of the Ancona branch.

A randomization technique based on a single sequence of random assignments is used. A list of random numbers generated by the computer is used and subject is assigned a number based on their order of inclusion in the study. According to this technique, the 195 subjects are randomly assigned to one of the 3 study groups.

At the end of the treatment and after 6 months, 1 year and 2 years, the patients will be contacted again to schedule subsequent follow-up visits and upgrades. During the follow-up period, patients will be monitored through telephone interviews once a month, in order to monitor their health state.

Recruitment will run from August 2019 to August 2021.

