### Data analysis

Continuous variables will be reported as either mean and standard deviation (SD) or median and interquartile range (IQR) on the basis of their distribution (assessed using Shapiro-Wilk test). Comparison of variables between groups will be performed by unpaired Student t test or Mann-Whitney U test according to their distribution. Categorical variables will be expressed as absolute number and percentage and statistical significance will be assessed by Chi-square test or Fisher Exact.

In a second step, the analysis of the follow-up data will be carried out in order to evaluate the effectiveness of the intervention. This analysis phase will involve the use of multivariate statistical techniques, in particular repeated measures analysis of variance (ANOVA), in order to compare the changes over time in the outcome measures between the intervention group and the control group. The statistical significant will be set at *p* < 0.05.

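### Data analysis section describes one intervention group against control, but three arms are randomised; how each device is compared with control is not defined

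*Protocol article*

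**What the plan says.** - **Design.** Trial design has patients "randomly divided into three groups, to receive a traditional rehabilitation program or" traditional therapy plus one of two devices. Recruitment repeats that "the 195 subjects are randomly assigned to one of the 3 study groups". Sample size gives "the total number required would be 195 subjects (65 for each arm").
- **Aim.** Under Study aims and objective, the primary aim is the effect on balance and gait "as a result of the use of the Tymo system or Walker View", by POMA, at end of treatment, 6 months, 1 year and 2 years.
- **Sizing model.** Sample size assumes "three groups and 5 repeated assessments (a baseline and 4 follow-ups) in an ANOVA model within-between interactions", with 80% power and alpha 0.05. It arrives at 153 subjects before dropout.
- **Analysis, first step.** Under Data analysis: "Comparison of variables between groups will be performed by unpaired Student t test or Mann-Whitney U test according to their distribution".
- **Analysis, second step.** Effectiveness is assigned to a repeated measures ANOVA, used to "compare the changes over time in the outcome measures between the intervention group and the control group". The threshold is p < 0.05, and no split or adjustment is given.

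**The concern.** The analysis text presupposes two groups and the design has three. This is a conflict between stated passages, so it is more than detail left to an analysis plan; a plan written faithfully to this section would carry the mismatch forward.

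Three analyses are compatible with some part of the article, and they answer different questions:

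1. Pool both devices against control. The Intervention section describes a balance and posture platform with games and a sensorised treadmill with gait feedback, which are different kinds of training.
2. Compare each device with control in separate two-group analyses at 0.05.
3. Test the three-group by time interaction used for sizing.

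The first can bury a benefit of one device. The second has no error control over two claims. The third can be significant because the devices differ from each other, or fade at different rates, and by itself it names no device as better than control. With the choice open, it could be made after the results are known.

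**Working it through.** **Inputs.** From Sample size: 3 groups, 5 assessments, power 80%, alpha 0.05, 153 evaluable, hence 153/3 = 51 per arm. The 10% effect size is read as Cohen's f = 0.10. Assumed because not stated: correlation between assessments 0.5, sphericity, and the SD effects in step 4.

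**1. Reproduce the plan's figure.** For a within-between interaction with k groups and m assessments, λ = f²·N·m/(1 − ρ), df1 = (k − 1)(m − 1), df2 = (N − k)(m − 1).
- N = 153: λ = 0.01 × 153 × 5/0.5 = 15.3; df1 = 2 × 4 = 8; df2 = 150 × 4 = 600; power 0.803.
- N = 150 gives 0.793, so 153 is the smallest multiple of three that reaches 80%.
- The required N depends on the correlation: 303 at 0, 213 at 0.3, 153 at 0.5, 93 at 0.7.

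The stated 153 is therefore the size for a joint three-group test with 8 numerator degrees of freedom.

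**2. Same model, one device against control.** k = 2, N = 2 × 51 = 102, f = 0.10 within the pair, ρ = 0.5: λ = 0.01 × 102 × 5/0.5 = 10.2; df1 = 4; df2 = 400.
- Power 0.72 at alpha 0.05; 80% needs 122 per pair (61 per arm).
- Power 0.62 at alpha 0.025; 80% needs 144 per pair (72 per arm).

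**3. Family-wise error if each device is tested at 0.05.** Equal arms and a shared control make the two test statistics correlate at 0.5. Simulation with 2 million draws gives about 0.09 (0.0975 if they were independent).

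**4. What pooling does.** Two-sided t test at one time point, SD 1, no baseline adjustment, noncentrality = δ/√(1/n₁ + 1/n₂). With one device effective at 0.5 SD and the other at zero, the pooled effect is 0.5/2 = 0.25 SD.
- Pooled, 102 v 51: 0.25/√(1/102 + 1/51) = 1.46; power 0.30 at 0.05.
- Effective device alone, 51 v 51: 0.5/√(2/51) = 2.52; power 0.71 at 0.05 and 0.60 at 0.025.
- Both devices effective at 0.5 SD, pooled: 0.5/√(1/102 + 1/51) = 2.92; power 0.83.

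Range over the assumed effect:

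| Effect (SD) | Pooled, one works | Own contrast, 0.025 | Pooled, both work |
|---|---|---|---|
| 0.4 | 0.21 | 0.40 | 0.64 |
| 0.5 | 0.30 | 0.60 | 0.83 |
| 0.6 | 0.41 | 0.77 | 0.94 |

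When one device works, its own contrast has nearly twice the pooled power even at the stricter threshold. When both work equally, pooling has more power than either device's contrast.

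**The case against.** **The singular may be loose drafting.** The Abstract and the Intervention section also use a singular technological group while describing two devices, and the Discussion speaks of experimental groups in the plural. Sample size and Data analysis both name repeated measures ANOVA, so a three-group model may well be intended. This stands as far as intent goes: the article does not say that the devices will be pooled. It does not remove the conflict, because Data analysis is the only passage that states the comparison, and it states a two-group one.

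**Contrasts and alpha sharing can sit in an analysis plan that is not shown.** This stands. The absence of a multiplicity rule is no finding on its own; what needs correction is the stated group structure.

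**The t test is not the effectiveness test.** Also correct. It belongs to a general first step, and effectiveness is assigned to the ANOVA. The wording of that second step carries the point by itself.

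**Two stronger readings are tempting, and the documents support neither.**
- A reader might infer that neither device gets a valid test against control. That does not follow: a t test, Mann-Whitney test or two-group repeated measures ANOVA of one device against control holds its nominal level. The contrast is undefined, not invalid.
- A reader might quote a family-wise error of 12.2%. That figure needs all three pairs tested without a gate. The article never states Tymo versus Walker View as a comparison. With exactly three groups, an omnibus test at 0.05 followed by unadjusted pairs keeps family-wise error at about 5%. The article states no such gate, but it does not state ungated tests either. About 9% is the figure for the two control contrasts when each is tested alone at 0.05.

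**Conclusion.** The point holds as a mismatch between the stated analysis and the design. Data analysis describes two groups where Trial design, Recruitment and Sample size have three, and it does not define how each device is compared with control, although the primary aim asks about the devices by name.

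The size depends on which reading is followed. Separate unadjusted contrasts carry a family-wise error of about 9%. Pooling cuts power from about 0.60 to about 0.30 if one device works at 0.5 SD, and gains power if both work. The joint interaction has its 80% power but does not identify a device. The SD effects are illustrations, since the article gives neither an SD nor an effect in SD units. The interaction figures rest on f = 0.10, correlation 0.5 and sphericity, under which the plan's 153 is reproduced.

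**What to change.** In Data analysis:

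- Write each intervention group in place of the single one, and fit one three-arm repeated measures model matching Sample size.
- Name Tymo versus control and Walker View versus control on POMA as the contrasts of interest, with Holm or Dunnett at overall 0.05. Make Tymo versus Walker View secondary.
- State the time point or points for these contrasts consistently with the primary aim, which covers four post-treatment assessments. Singling out the end of treatment would change that aim and should be a deliberate decision. If every time point is confirmatory, the family is 2 × 4 = 8 contrasts and the adjustment must cover them.
- For first-step comparisons across all arms, use one-way ANOVA or Kruskal-Wallis.

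In Sample size, say that 80% power refers to the joint interaction, and give the power for a device contrast (0.72 at 0.05 and 0.62 at 0.025 for the interaction under the assumptions above).

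No data collection changes. The costs are a stricter threshold per device and an open statement that the device contrasts have less than 80% power at 51 per arm. Trial status reports that data collection is ongoing, so the change should be made before any between-group results are seen.

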## Discussion

The aim of the present study protocol is to evaluate an innovative rehabilitation treatment of the older adults with Parkinson’s disease, designed to improve the gait and to reduce the risk of falling. This innovative rehabilitation program involves two different robotic devices that work using visual or auditory feedback in order to correct wrong postural or gait patterns. Moreover, further evaluations, such as length and asymmetry of the step, walking and functional status and acceptance of the technology will be carried to underline the efficacy of this innovative treatment.

The study population will be given different questionnaires (Mini-Mental State Examination, Rankin scale, Barthel Index, Functional Ambulation Categories, Hoehn and Yahr Scale, SF-12 Health Survey, Tinetti’s Scale, Motricity index, Short Falls Efficacy Scale – International, Psychosocial Impact of Assistive Devices Scale, Assistive Device Predisposition Assessment, Geriatric Depression scale 5-items version, Clinical Dementia Rating Scale, General Data Protection Regulation) that take into consideration different aspects of the patient’s health status.

We focus on PD patients with mild subjective cognitive complaints that are expected to have the opportunity to employ significant neural plasticity in response to motor rehabilitation program with robotic devices. In order to analyze between-group differences in control group, treated only with traditional rehabilitation, and experimental groups, treated with robotic devices (Tymo system or Walker View), we will randomize the included patients to have results as reliable and error-free as possible.

Another important aspect of this protocol is the check of the results obtained not only at the end of the treatment but also in the long term, foreseeing 3 follow-up, at 6 months, 1 year and 2 years from the end of the rehabilitation program.

The dissemination program will involve peer-reviewed journal and national and international conferences. Moreover, the results will be disseminated to all participants.

## Data Availability

The datasets generated, used and analyzed during the trial and its preceding pilot trial are or will be available from the corresponding author upon reasonable request.

## Abbreviations

ATDPA: Assistive Device Predisposition Assessment
BI: Barthel Index
CDR: Clinical Dementia Rating Scale
FAC: Functional Ambulation Categories
FES-I-Short: Short Falls Efficacy Scale - International
GDPR: General Data Protection Regulation
GDS: Geriatric Depression scale 5-items version
MI: Motricity index
MMSE: Mini-Mental State Examination
PD: Parkinson’s disease
PIADS: Psychosocial Impact of Assistive Devices Scale
POMA: Tinetti’s Scale or Performance-Oriented Mobility Assessment
RA: Rankin scale
SF-12: SF-12 Health Survey
SHY: Hoehn and Yahr Scale
